## Abstract

**Background:**

A recently published systematic review indicated superiority of duodenum-preserving techniques when compared with pancreatoduodenectomy, for the treatment of patients with chronic pancreatitis in the head of the gland. A multicentre randomised trial to confirm these results is needed.

**Methods/Design:**

ChroPac aims to investigate differences in quality of life, mortality and morbidity during 24 months after surgery (duodenum-preserving pancreatic head resection versus pancreatoduodenectomy) in patients with chronic pancreatitis of the pancreatic head.

ChroPac is a randomised, controlled, observer and patient blinded multicentre surgical trial with two parallel comparison groups. The primary outcome measure will be the average quality of life during 24 months after surgery. Statistical analysis is based on the intention-to-treat population. Analysis of covariance will be applied for the intervention group comparison adjusting for age, centre and quality of life before surgery. Level of significance is set at 5% (two-sided) and sample size (n = 100 per group) is determined to assure a power of 90%.

**Discussion:**

The ChroPac trial will explore important outcomes from different perspectives (e.g. surgeon, patient, health care system). Its pragmatic approach promises high external validity allowing a comprehensive evaluation of the surgical strategy for treatment of patients with chronic pancreatitis.

**Trial registration:**

Controlled-trials.com ISRCTN38973832

## Background

### Rationale of the trial

Chronic pancreatitis (CP) is defined as a continuous inflammatory process causing permanent structural damage ultimately resulting in impairment of the gland's exocrine and endocrine function [1,2]. The most important causative agent is alcohol. Patients with CP who present with inflammatory pancreatic head enlargement, commonly require pancreatic head resection due to development of local complications (e. g. stenosis of the common bile duct and/or main pancreatic duct, duodenal obstruction, compression of retropancreatic vessels), suspicion of malignancy, and most commonly intractable pain [3,4]. Pancreatoduodenectomy (PD), i.e. the classical Whipple (CW) and subsequently the pylorus-preserving Whipple (PPW) procedure has served as primary surgical procedures for removal of the pancreatic head in patients with CP and pancreatic head enlargement for many years. However, PD is reported to have unsatisfactory outcome in terms of late morbidity; including high incidence of postoperative diabetes mellitus of up to 48%, attributed to the extensive resection of the duodenum and a larger portion of the pancreas [5]. In order to preserve the duodenum and limit resection of the pancreatic tissue to a minimum, the duodenum-preserving pancreatic head resection (DPPHR) was introduced by H. G. Beger in 1972 [6,7]. While the Beger procedure selectively removes the pancreatic head, two modifications of this procedure were developed in order to prevent dissection of the pancreas above the portal and superior mesenteric vein, a potential source of haemorrhage, particularly in case of portal hypertension: The Frey procedure consists of a local resection of the pancreatic head, which is combined with lateral pancreaticojejunostomy; in the Berne procedure the pancreatic head is resected subtotally, leaving a narrow layer of pancreatic tissue towards the duodenum and the retropancreatic vessels [4,8,9] (Figure 1).

**Figure 1 F1:**
[figure not shown]
**Techniques of pancreatoduodenectomy and duodenum-preserving pancreatic head resection (DPPHR)**. (A) Classical Whipple procedure after resection and reconstruction with pancreaticojejunostomy, bilio-digestive anastomosis and gastrojejunostomy. (B) DPPHR according to Beger: Dissection of the pancreas above the portal vein, escavation of the pancreatic head and incision of the common bile duct. Reconstruction s accomplished by two pancreaticojejunostomies (corpus and pancreatic head). (C) DPPHR, Berne modification: Excavation of the pancreatic head and incision of the common bile duct without dissection of the pancreas above the portal vein. Reconstruction is accomplished by one single side-to-side pancreatcojejunostomy. (D) DPPHR, Frey modification: circumscripted excavation of the pancreatic head and longitudinal incision of the pancreatic duct. Reconstruction is accomplished by pancreaticojejunostomy.

### Preliminary data

A recently published randomised trial demonstrated superiority of surgical treatment (i. e. pancreaticojejunostomy) as compared with endoscopic drainage in patients with chronic pancreatitis and a distal pancreatic duct obstruction without an inflammatory mass, respectively [10]. Moreover, an up-to-date systematic review with meta-analysis indicated superiority of duodenum-preserving pancreatic head resection (DPPHR) compared with pancreatoduodenectomy (PD) in terms of several intra- (blood replacement) and postoperative (exocrine insufficiency, length of hospital stay, weight gain and occupational rehabilitation) outcome parameters as well as quality of life (QoL) [11]. However, this potential superiority of DPPHR is currently based on small hypothesis driven clinical trials performed in a single-institution setting and may be distorted by as well random error due to small sample sizes, as systematic sources of bias such as allocation concealment, standardization of study interventions, definition of outcome parameters, consistency of follow-up, and blinded outcome assessment. Large multicenter randomised trials comparing the two main strategies (DPPHR vs. PD) focussing on both the surgeons and patients perspectives are still missing.

### Objective

ChroPac aims to investigate differences in QoL during 24 months after surgery of DPPHR versus PD and mortality as well as general and pancreas-associated postoperative morbidity.

### Trial locations

ChroPac will be performed in thirteen trial sites with expertise for pancreatic surgery. Most of the participants were involved in a former multicentre-trial surgical trial for pancreatic left resection (DISPACT Trial, ISRCTN 18452029) carried out by the Study Centre of the German Surgical Society (SDGC). Thus the ChroPac trial group consists of international pancreatic surgeons at high-volume centres who also have expertise in trial conduction.

## Methods/Design

### Trial population and eligibility criteria

All patients scheduled for primary elective surgery for chronic head-pancreatitis will be eligible, assuming their ability to understand the character and individual consequences of participation as well as written informed consent. Patients participating in another interventional trial with potential interference of intervention (e.g. trials evaluating alternative perioperative analgetic regimens, application of octreotide etc.) and outcome (e.g. trials focussing on QoL) will be excluded.

### Sample size

A total of 200 patients will be randomised and included in the analysis.

### Type of Trial

Randomised, controlled, observer and patient blinded multicentre surgical trial with two parallel comparison groups.

### Recruitment and trial timeline

13 centres with high-level expertise for pancreatic surgery will contribute to recruitment of study patients. The duration of the trial for each participant is expected to be about 2 years. The duration of the overall trial is expected to be 5 years, including prearrangement and analysis. Recruitment of participants started in April 2009. The process of the trial conduct is illustrated in Figure 2.

**Figure 2 F2:**
[figure not shown]
**ChroPac study flow**.

### Randomisation

In order to achieve comparable intervention-groups, patients will be allocated concealed by preoperative randomisation at the day of surgery using a centralised web based tool http://www.randomizer.at. Block randomisation will be performed for each centre to achieve equal group sizes per centre.

### Blinding

Patients and outcome assessors will be blinded for the trial intervention.

### Interventions

#### Trial-intervention

Any surgical technique that removes inflamed pancreatic tissue of the head without resection of the duodenum (e.g. Begers, Frey or Berne procedure).

#### Control-Intervention

PPW or CW.

The procedures in both groups can be chosen according to preference of the surgeon which is based on his/her personal knowledge, skills and mainly the anatomical situation of the patient, since ChroPac aims to compare general surgical strategies rather than to compare certain modifications of the surgical procedure. Each participating centre performs the procedure according to local standards and according to the anatomical situation.

The schedule of trial interventions is presented in Table 1.

**Table 1 T1:** Study visits of the ChroPac-Trial

Visit	Visit 1 (Screening)	Visit 2 (Day of surgery)	Visit 3 (Day of discharge)	Visit 4 (6 months post OP)	Visit 5 (12 months post OP)	Visit 6 (24 months post OP)
Demographics and baseline clinical data	X					

Inclusion/exclusion	X					

Randomisation		X				

Surgical intervention		X				

Assessment of secondary outcome measures and safety		X	X	X	X	X

Quality of Life	X			X	X	X

Tissue and blood sampling		X				

### Risks

No additional risks for study patients are awaited, since all surgical procedures carried out within ChroPac represent clinically established standard methods of treatment of chronic pancreatitis.

### Outcomes

The primary outcome measure of this trial is the average QoL during 24 months after surgery, measured 6, 12 and 24 months after surgery by the EORTC QLQ-C30 scale „physical functioning“ (PF-2). Secondary outcomes of: mortality, general (wound infection, pulmonary infection) and pancreas-associated postoperative morbidity (pancreatic fistula, delayed gastric emptying), operation time, intraoperative blood loss, initial postoperative hospital stay, reoperation, hospital stay related due to chronic pancreatitis within 24 months after randomisation, weight gain, development of exocrine insufficiency and new onset of diabetes mellitus will be assessed (Table 2). All outcome variables will be evaluated according to internationally accepted standards and scoring systems if available, i.e. the consensus definitions for pancreatic fistula and delayed gastric emptying of the International Study Group of Pancreatic Surgery (ISGPS) [12,13].

**Table 2 T2:** Summary and definitions of secondary outcomes

Summary and definitions secondary outcomes	
**Mortality**	Death due to any cause at any time during the follow-up period including reason.

**General morbidity**	
▪ Wound infection	Surgical site infections will be assessed at discharge and 6 months after surgery, divided into superficial and deep incisional surgical site infection according to the Center for Disease Control and Prevention definition [22].
▪ Pulmonary infection	Post-Op-Pulmonary infection will be assessed, at discharge and 6 months and is defined according to local standards:
	Infection of the lung with either evidence of increased infection parameters (CRP > 2 mg/dl and/or leukocytes > 10 0000/ml) which are not caused by a different pathologic process or evidence of pulmonary infiltration in the chest x-ray, requiring antibiotic therapy.

**Pancreas associated postoperative morbidity**	
▪ Postoperative Pancreatic fistula [12]	Any abnormal communication between the pancreatic ductal epithelium and another epithelial surface containing pancreas-derived, enzyme-rich fluid.
	It should satisfy the following criteria:
	• output through an operatively placed drain or a subsequently placed percutaneous drain of any measurable volume of drain fluid
	• on or after postoperative day 3
	• amylase content in fluid greater than three times the upper normal serum value.
	Since only longstanding observation will confirm the diagnosis, it is necessary to distinguish and to grade the POPF as grades A, B and C after clinical recovery is complete.
	Grade A:
	• Without clinical impact
	• Oral nutrition
	• No antibiotics
	• No somatostatin analogues
	• No peripancreatic fluid collection
	• No delay in hospital discharge
	Grade B:
	• Clinically relevant
	• Partial/total parenteral/enteral nutrition
	• Peripancreatic collection possible
	• Abdominal pain, fever, and/or leucocytosis possible
	• Antibiotics and somatostatin analogues may be necessary
	• Delay in hospital discharge or readmission may be required
	Grade C:
	• Clinical stability maybe borderline
	• Treatment in an intensive care unit in many cases
	• Total parenteral/enteral nutrition
	• Intravenous antibiotics and somatostatin analogues necessary
	• Worrisome peripancreatic fluid collection that requires percutaneous drainage
	• Extended hospital stay
	• Often associated complications and postoperative mortality possible
▪ Delayed gastric emptying [13]	Delayed gastric emptying represents the inability to return to a standard diet by the end of the first postoperative week and includes prolonged nasogastric intubation of the patient. Three different grades (A, B, and C) were defined based on the impact of the clinical course and on postoperative management.

**Operation time**	From skin incision to closure of wound [min].

**Blood loss assessed by surgeons and anesthesists**	Intraoperative blood loss [ml].

**Hospital stay**	
▪ Initial postoperative hospital stay after randomization	Day of operation until day of discharge.
▪ Total hospital stay due to chronic pancreatitis within 24 months after randomization	Total amount of hospital days after randomization for any treatment due to chronic pancreatitis within 24 months.

**Reoperation due to recurrence of chronic pancreatitis**	Any surgical intervention for treatment of the pancreas at any time during the follow-up period.

**Weight gain**	Body weight [kg] assessed at all visits.

**New onset of diabetes mellitus requiring treatment**	Any continuous treatment (drugs) of diabetes lasting for 12 months.

**Development of exocrine insufficiency (continuous supplement of pancreatic enzymes necessary)**	Any continuous treatment (drugs) of exocrine insufficiency lasting for 12 months.

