### Safety evaluation and reporting of adverse events

Analysis of safety related data is performed with respect to frequency of serious adverse events, frequency of serious adverse events stratified by causality and frequency of morbidity in both treatment groups.

From the day the patient has signed informed consent until the regular end of trial at 24 months follow-up or until premature withdrawal of the patient, all serious adverse events will be documented on a "serious adverse event form" available in the investigator site file. A serious adverse event will be defined as an event, that results in death, is immediately life-threatening, requires or prolongs hospitalization or results in persistent or significant disability or incapacity. Serious adverse events will be classified to intensity (mild, moderate, severe), outcome (ongoing, recovered completely, recovered with sequelae, death, unknown) and causality (unrelated; possibly, probably or definitely related to trial intervention; not assessable). The assessment is based on surgical findings and the clinical course of the patient. It needs to be done by the investigators in the participating trial centres. They will be furnished with written recommendations on how to assess causality with trial intervention within the ChroPac trial.

Serious adverse events have to be reported by the attending physician to the principal investigator within 24 hours after the SAE becomes known.

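### The 12-month treatment rule for new diabetes and exocrine insufficiency stops any treatment started after month 12 of a 24-month follow-up from counting as a case

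*Protocol article*

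**What the plan says.** Table 2 (Summary and definitions of secondary outcomes) fixes both case definitions by duration of drug treatment:

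- New-onset diabetes: "Any continuous treatment (drugs) of diabetes lasting for 12 months".
- Development of exocrine insufficiency: "Any continuous treatment (drugs) of exocrine insufficiency lasting for 12 months".

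Follow-up is set in three places. Recruitment and trial timeline: "The duration of the trial for each participant is expected to be about 2 years". The safety section documents serious adverse events "until the regular end of trial at 24 months follow-up or until premature withdrawal of the patient". In Table 1, the row "Assessment of secondary outcome measures and safety" is ticked on the day of surgery, at discharge, and at 6, 12 and 24 months, and there is no later visit.

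Other rows of Table 2 carry no such restriction. Reoperation is "Any surgical intervention for treatment of the pancreas at any time during the follow-up period". Mortality also covers the whole follow-up, and disease-related hospital days are totalled over 24 months.

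The Outcomes section lists both conditions as secondary ("weight gain, development of exocrine insufficiency and new onset of diabetes mellitus will be assessed"), and the Analysis section treats secondary outcomes descriptively. The Rationale criticises PD for its late morbidity and gives as its example a "high incidence of postoperative diabetes mellitus of up to 48"%.

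**The concern.** A case needs 12 months of continuous treatment, and each patient is observed for 24 months. Onset in the second half of follow-up therefore cannot satisfy the definition before observation stops, and the article gives no rule for treatment that is running at month 24 but has lasted less than 12 months. This comes from a definition the article states, not from a detail it leaves out.

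At stake is how the two rates will be read. The Abstract gives the aim as comparing quality of life, mortality and morbidity during 24 months, and the Rationale treats diabetes as a late consequence of PD. Preliminary data and Discussion both list exocrine insufficiency among the outcomes on which duodenum-preserving resection (DPPHR) appeared better. A count closed to late onsets fits a late-morbidity question poorly. If one operation tends to produce later onset than the other, the arm with later onset looks better than it is.

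**Working it through.** **Plan's own figure.** The article states no expected 24-month rate and no calculation for either outcome, so there is none to reproduce. Its only computed figure, 86 per group, belongs to the primary outcome. It reproduces (10-point difference, SD 20, two-sided 5%, 90% power: 85.03 by the t-test calculation, rounded up to 86) and is not in question here.

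**Step 1: the cut-off.** Inputs: required treatment duration 12 months (Table 2); end of observation 24 months (Table 1, timeline, safety section).

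Latest qualifying start = 24 − 12 = month 12.

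Starts in months 12 to 24, half of the follow-up window, cannot qualify. This step needs no assumption beyond the stated definition and schedule.

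**Step 2: size of the undercount in one arm.** Let f be the share of 24-month onsets that start after month 12. The article does not give f, so it is **assumed**. Counted rate = true rate × (1 − f). The true rate is set for illustration at 48%, the upper figure in the Rationale.

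| Assumed f | Counted rate |
|---|---|
| 10% | 0.48 × 0.90 = 43.2% |
| 25% | 0.48 × 0.75 = 36.0% |
| 50% (onset uniform over 24 months) | 0.48 × 0.50 = 24.0% |

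Under an assumed constant hazard reaching 48% at 24 months, the 12-month incidence is 1 − √(1 − 0.48) = 27.9%. The missed share is 1 − 0.279/0.48 = about 42%.

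**Step 3: both arms, same timing.** PD is set at 48% and the DPPHR rate is **assumed**. The difference shrinks by the factor (1 − f), while the ratio of the rates does not change.

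| Assumed DPPHR rate | True difference | f = 10% | f = 25% | f = 50% |
|---|---|---|---|---|
| 24% | 24.0 points | 21.6 | 18.0 | 12.0 |
| 36% | 12.0 points | 10.8 | 9.0 | 6.0 |

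**Step 4: both arms, different timing.** True rates are taken as 48% (PD) and 36% (DPPHR), a difference of 12.0 points.

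- 10% late in PD, 40% late in DPPHR: 0.48 × 0.90 = 43.2% against 0.36 × 0.60 = 21.6%. The counted difference is 21.6 points, exaggerated.
- 40% late in PD, 10% late in DPPHR: 0.48 × 0.60 = 28.8% against 0.36 × 0.90 = 32.4%. The counted difference is −3.6 points, reversed.

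These splits only show that the bias has no fixed direction. They are not estimates.

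**The case against.** A duration criterion has a sound purpose: it screens out transient postoperative treatment and fits the requirement in the exocrine row's label for continuous enzyme supplementation. Neither row claims a 24-month cumulative incidence. Table 2 files diabetes and exocrine insufficiency outside its general and pancreas-associated morbidity headings. The Analysis section also plans to describe the time course of secondary outcomes, which might reveal later treatment. And the Rationale attributes diabetes after PD to the extent of resection, which is compatible with early onset and a small loss.

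Much of this stands as a limit on the point. It does not remove the point. The 12-month rule cannot tell transient treatment from persistent treatment that began late. The Rationale itself calls diabetes late morbidity. A time-course display built on the same definition would still leave out late starts as cases.

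Some stronger readings are tempting, but the article does not support them:

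- *Late onsets go unrecorded.* Secondary outcomes are assessed at the 24-month visit, so a late start can be noted. It only fails to qualify.
- *Patients already treated before surgery are counted.* The row labels speak of new onset and development, which exclude prevalent cases, and baseline clinical data are collected at screening.
- *Patients who die or withdraw before completing 12 months of treatment are scored as non-events.* The article does not say so. Their handling, like the exact denominator, is ordinary content of an analysis plan.

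**Conclusion.** The point holds. Under Table 2 as written, treatment started after month 12 can never become a case of new diabetes or exocrine insufficiency, so the rates describe onsets in about the first year of a two-year trial. The cut-off is exact, subject to visit timing around month 24. The size of the loss is not known. A true 48% is counted as anything from 43.2% to 24.0% when 10% to 50% of onsets are late, and the loss is smaller still if nearly all onsets follow soon after surgery. Neither the size nor the direction of any bias between the arms can be derived from the article.

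A reader might infer that the rule manufactures a specific false advantage for one operation, or that it undermines the trial's main conclusion. The first would need onset timing by arm, which the article does not give. The second fails because these are two of many secondary outcomes with no stated hierarchy, analysed descriptively, and the primary outcome, its test and the sample size are untouched. The issue is moderate and not a must-fix.

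**What to change.** In Table 2, keep the 12-month-duration definition and add a second count for each condition: drug treatment that starts after surgery and is still ongoing at the 24-month visit is also a case, even if it has lasted less than 12 months. Record the treatment start date in the eCRF at the existing visits. Report this count to month 24 beside the 12-month version, by arm, so that readers can see how many cases depend on the duration rule.

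The cost is a wording change and one date field per condition. It adds no visit and leaves the primary analysis and sample size as they are. The downside is that some short-lived treatment begun near month 24 will be counted without evidence that it persists, which is why both versions should be shown.

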### Data management

All protocol-required information for the clinical data collected during the trial must be entered by the investigator, or by a designated representative, in the eCRF. The investigator is responsible for ensuring that all sections of the eCRF are completed correctly and that entries can be verified against source data. Any entry and correction in the Remote Data Entry System will be recorded automatically in an audit file. Once the documentation of a patient is completed and checked for plausibility the investigator is asked to date and sign it via electronic identification. Documentation of quality of life questionnaires will be done on paperbased CRFs.

Double data entry will be accomplished in order to ensure completeness, validity and plausibility of trial data.

